#### Safety outcomes

2.8.3

Laboratory liver and renal function tests will be conducted on all participants at the screening phase (week 0) and post-treatment phase (week 4) to evaluate the safety of the SYM granules. Vital signs will be examined at each visit. Investigators will conduct causality assessment to all the reported adverse events including subjective or objective symptoms of participants at every visit. All adverse events will be recorded in the CRFs regardless of the relationship with the intervention provided. Investigators will ensure that all participants with adverse reactions receive appropriate medical treatment and follow-up until symptoms are resolved.

#### Study feasibility outcomes

2.8.4

The recruitment rate (a percentage of the number of enrolled participants relative to the total number of screened participants), adherence rate (a percentage of the number of participants taking 70% of the investigational product relative to the total number of participants), and completion rate (a percentage of the number of participants who complete the trial without dropping out relative to the total number of participants) will be calculated to determine whether a confirmatory, full-scale, randomized controlled trial is feasible.

### Sample size

2.9

There has been no clinical trial to evaluate the effects of SYM on individuals with both insomnia disorder and prehypertension or stage 1 hypertension. Therefore, a formal sample size calculation was not performed because this study will evaluate the feasibility of subsequent confirmatory randomized controlled trials. With reference to a study that recommends a minimum of 12 participants per group in a pilot study in the biological science field,^[40]^ a total of 30 participants were deemed necessary for each group of 15, anticipating a 20% dropout rate.

### Statistical analysis

2.10

All statistical analyses will be conducted by an independent statistician using SPSS Statistics for Windows, Version 24.0 (IBM Corp., NY, USA). According to the intention-to-treatment principle, which analyzes all participants who have been randomized, all data obtained from participants who undergo an outcome measurement at least once after randomization will be included in the effectiveness analysis. Per protocol set (PPS) analysis will also be conducted if necessary, including only participants who complete the entire process as described in the protocol with no significant violations. Safety analysis will include all data obtained from participants who take the investigational product at least once.

For each group, categorical data will be presented as frequency and percentage, and continuous data as mean and 95% confidence intervals or median according to the distribution of the data. Any statistical differences between 2 groups will be tested by using the Chi-Squared test or Fisher exact test for categorical data and using the Independent *t* test or Wilcoxon rank sum test for continuous data.

The primary outcome is the total ISI score at 4 weeks post-treatment. A two-sided test with a significance level of 0.5 will be performed using an analysis of covariance with the baseline as the covariate and the treatment group as fixed factors. In addition, the analysis can be performed by setting variables that show statistically significant differences in demographic or social characteristics or variables that can affect insomnia or blood pressure as covariates. The last observation carried forward method will be used for missing data. If necessary, subgroup analysis may be performed by categorizing the baseline characteristics of the participants at the screening visit or the baseline visit. Intra-group changes in the outcome measures from baseline to post-treatment will be analyzed using the Chi-square test or Fisher exact test for categorical data and the paired *t* test or Wilcoxon signed rank test for continuous data. Furthermore, we will use a mixed effect model to identify trend changes.

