### Interventions

2.7

Participants in the SYM group will receive 3.0 g SYM granules twice a day before or between meals for 4 weeks. The dosage is based on the regimen approved by the Korea Ministry of Food and Drug Safety. We will use Kracie Sihogayonggolmoryeo-tang Extract Fine Granules manufactured by Kracie Pharma Korea Co., Ltd (Seoul, Republic of Korea) in accordance with good manufacturing practice standards. The SYM granule is a light brown-brown mixture of the hot water extracts of 11 medicinal plants: *Bupleuri Radix* 5.0 g, *Fossilia Ossis Mastodi* 2.5 g, *Ostreae Testa* 2.5 g, *Scutellariae Radix* 2.5 g, *Cinnamomi Ramulus* 3.0 g*, Poria Sclerotium* 3.0 g*, Zingiberis Rhizoma Recens* 0.8 g, *Zizyphi Fructus* 2.5 g*, Rhei Radix et Rhizoma* 1.0 g*, Pinelliae Tuber* 4.0 g, and *Ginseng Radix* 2.5 g per 1 day. A pharmacist will be responsible for the storage, dispensation, and quality control of the SYM granules. If there are any adverse events during the study period, investigators will take appropriate action depending on the severity of the adverse event and the causal relationship with the investigational product.

The wait-list group will not receive SYM granules and will be instructed to maintain conventional care during the study period. The participants in this group will receive 2 weeks of SYM granules as compensatory treatment after the wait-list period if desired under the judgment of Korean medicine doctors, although this will not be included in the analysis. All participants in both groups will be educated and provided with brochures on maintaining sleep hygiene and hypertension lifestyle modification including diet and exercise during the study period.

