## Discussion

3

This is a study protocol for a randomized, wait-list controlled, parallel, pilot clinical trial evaluating the effect of SYM on patients with both insomnia disorder and prehypertension or stage 1 hypertension. We will evaluate the preliminary effectiveness and safety of 4-week administration of SYM compared to lifestyle modification only and assess the feasibility of large-scale randomized controlled trials.

Insomnia and high blood pressure are very common diseases worldwide, and the economic burden is substantial.^[2,41]^ In particular, the 2 diseases have been reported to be associated with each other.^[5–8]^ For patients with prehypertension or stage 1 hypertension in particular, active lifestyle modification is recommended before medication.^[19,20]^ If patients with insomnia disorders and prehypertension or stage 1 hypertension taking sleep sedatives have elevated blood pressure and therefore take antihypertensive drugs, there may be risks associated with the combination of multiple drugs. However, there is no recommended conventional medication for treating both insomnia and hypertension.

Herbal medicine contains multiple active components that act on multiple targets and therefore has the potential to overcome the limitations of conventional medication with a single active constituent.^[12]^ SYM is an herbal formula that has been approved by the Korea Ministry of Food and Drug Safety and is commercially marketed for symptoms that accompany hypertension (insomnia, anxiety, and palpitation), nervousness, and morbid night crying of babies. Because SYM is an herbal medicine that is already used for treating patients with insomnia disorder and hypertension, the effectiveness and safety have been proven in historical medical literature with long-term empirical evidence. Our study will provide scientific evidence for the effectiveness and safety of SYM through a clinical trial in accordance with scientific procedures. In addition, SYM can be expected to improve not only insomnia but also blood pressure, which may reduce the risk of polypharmacy in the future.

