Nevertheless, to the best of our knowledge, this is the first study evaluating the feasibility and effect of SYM on insomnia patients with prehypertension or stage 1 hypertension using validated questionnaires. Though hypertension itself is not a major problem, it can increase the risk of developing life-threatening cerebrovascular diseases.^[43]^ Insomnia disorder is also known to increase the risk of cardiovascular diseases.^[4]^ Therefore, we will evaluate the degree of atherosclerosis by measuring baPWV, ABI, hs-CRP, ESR, homocysteine, and fibrinogen as markers of cardio-cerebrovascular disease during the study period to investigate the effects of SYM on atherosclerosis. If the treatment effect and safety of SYM compared with the wait-list control is demonstrated through this pilot study, the findings are expected to provide a base for large-scale, confirmatory, multicenter, high-quality randomized control trials to draw definite conclusions regarding the efficacy and safety of SYM for patients with concurrent insomnia disorder and hypertension. Furthermore, the results may provide stronger evidence of SYM as a treatment option for insomnia disorder with hypertension for clinicians, patients, and researchers.

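### The safety set admits only participants who took SYM, so the untreated wait-list arm drops out and the safety comparison described in the Discussion cannot be made

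*Protocol article*

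**What the plan says.** The rule for the safety set is one sentence in section 2.10 (Statistical analysis): "Safety analysis will include all data obtained from participants who take the investigational product at least once".

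Section 2.7 (Interventions) describes the control: "The wait-list group will not receive SYM granules and will be instructed to maintain conventional care during the study period". The Discussion explains that no placebo granule could be made. Wait-list participants may have 2 weeks of SYM after the wait-list period, and section 2.7 adds, "although this will not be included in the analysis".

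Section 2.8.3 (Safety outcomes) collects safety data without regard to arm. On laboratory tests: "Laboratory liver and renal function tests will be conducted on all participants at the screening phase (week 0) and post-treatment phase (week 4". On adverse events: "All adverse events will be recorded in the CRFs regardless of the relationship with the intervention provided". Vital signs are taken at each visit.

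The Discussion describes safety as a comparison in two places. Near its start: "We will evaluate the preliminary effectiveness and safety of 4-week administration of SYM compared to lifestyle modification only". In its last paragraph: "If the treatment effect and safety of SYM compared with the wait-list control is demonstrated through this pilot study".

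**The concern.** A rule of at least one dose suits a trial in which every arm receives a study product. Here one arm receives nothing, so the rule removes that whole arm from the analysis of adverse events and of liver and renal tests.

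What is at stake is the only concurrent reference for safety. Over six weeks, people with insomnia and raised blood pressure will report symptoms whatever they take, and liver and renal values will vary between week 0 and week 4. Without the wait-list column, a reader cannot tell how much of what is seen in the SYM arm is background. The article collects the data that would answer this, says that it will make the comparison, and then fixes an analysis set in which the comparison has only one side.

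**Working it through.** **1. Group size.** Section 2.9 takes a minimum of 12 per group and 20% dropout: 12 / (1 − 0.20) = 15 per group, 2 × 15 = 30 in total. This reproduces the stated figure.

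**2. Who meets the safety rule.**

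| Arm | Randomised | SYM in study period (2.7) | Safety data collected (2.8.3) | In safety set (2.10) |
|---|---|---|---|---|
| SYM | 15 | yes | yes | up to 15 |
| Wait-list | 15 | no, and no placebo | yes | 0 |

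Up to 15 of 30 randomised participants (15/30 = 50%) fall outside the safety analysis. No between-group difference can be formed from 15 against 0.

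**3. Whether another passage restores the control arm.** Section 2.10 goes on: "Any statistical differences between 2 groups will be tested by using the Chi-Squared test or Fisher exact test for categorical data". This is a general rule for comparing the groups. It needs two groups to run, and the safety set supplies one. No other passage defines a safety set that includes the wait-list arm.

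**4. What is affected.** Blood pressure is a secondary outcome (section 2.8.2). The effectiveness analysis takes in any randomised participant with at least one outcome measurement after randomisation, so wait-list blood pressure is analysed there. The gap concerns mainly adverse events and the liver and renal tests. Those tests are scheduled at week 0 and week 4 only, so the laboratory question covers that interval and not the full six weeks.

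**5. What the repair would buy.** With both arms in the set there are up to 15 against 15. If the wait-list has no events and the SYM arm has k, the two-sided Fisher exact p-value is 2 × C(15,k) / C(30,k):
- k = 4: 2 × 1,365 / 27,405 = 0.100
- k = 5: 2 × 3,003 / 142,506 = 0.042

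Power of that test, at an assumed two-sided level of 0.05 and assumed event rates (the article gives none for safety):

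| SYM | Wait-list | Power |
|---|---|---|
| 30% | 10% | 15% |
| 40% | 10% | 33% |
| 50% | 10% | 54% |

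The restored comparison can describe differences but is poorly placed to test them.

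**The case against.** The strongest reply is that the article's formal aims never promise a between-group safety contrast. The Abstract and Introduction speak of exploring the safety of SYM, and section 2.8.3 says the laboratory tests serve to evaluate the safety of the granules. Both comparative statements are in the Discussion, and the one in the last paragraph is a conditional about future trials. On this view, section 2.10 carries a loosely adapted standard definition, and the general between-group tests show that two groups were meant. The set also touches neither the primary outcome nor the feasibility outcomes.

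Part of this stands. The mismatch is between section 2.10 and the Discussion, not between two commitments in the Methods. But the earlier Discussion sentence is an unconditional statement of what will be done, and section 2.8.3 collects the control data that it needs. Read naturally, section 2.10 prevents that comparison. An analysis plan that follows the sentence inherits the problem; one that does not follow it contradicts the article.

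A reader might also infer more than the documents support:
- *That wait-list safety data are thrown away.* They are not. All adverse events go into the case report forms, and wait-list blood pressure is analysed as an outcome.
- *That wait-list participants who later take SYM will be pooled with the randomised SYM arm.* Taken alone, the at-least-once wording would admit them. Section 2.7 keeps that treatment out of the analysis, and the specific exclusion governs. Section 2.10 merely fails to repeat it.
- *That the uncertainty around zero events measures this defect.* With 0 events in 15, the exact two-sided 95% upper limit is 1 − 0.025^(1/15) = 21.8%. That limit applies to the SYM arm however the set is defined, so it reflects the size of the pilot.

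**Conclusion.** The point holds in a bounded form. As written, the safety set has at most 15 SYM and 0 wait-list participants. The comparison of safety with lifestyle modification only, or with the wait-list, cannot be made from it. Adverse events and week 0 to 4 liver and renal changes in the SYM arm would be reported with no concurrent reference.

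This rests on reading the sentence in section 2.10 as the definition of the set, which is its natural reading, and on full recruitment of 15 per arm. Dropout would change the first count but not the zero. It does not rest on the assumed event rates, which show only that the repaired comparison would remain descriptive. A reader might infer that adding the control arm would let this pilot demonstrate safety; at this sample size it would not. The sentence is wrong for this design and should be corrected before the analysis.

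**What to change.** In section 2.10, define the safety set as all randomised participants, grouped by treatment received during the study period, weeks 0 to 6 (SYM or none). Tabulate adverse events and week 0 to 4 laboratory changes in both arms with 95% confidence intervals, and label the comparison descriptive.

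Add one sentence, consistent with section 2.7, saying that SYM taken after the wait-list period is not pooled into this set and that any events recorded then are listed separately.

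The cost is a few sentences and one more column in the safety tables. No extra visits, tests or participants are needed, because section 2.8.3 already collects these data in both arms.

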### Trial design

2.1

A prospective, randomized, wait-list controlled, parallel, pilot clinical trial will be performed at the Daejeon Korean Medicine Hospital of Daejeon University (Daejeon, Republic of Korea). The trial period will include 4 weeks of medication (twice a day) and 2 weeks of follow-up. The study procedure is summarized in Figure 1 and Table 1. A total of 30 participants will be included and they will be randomly assigned to a SYM group or a wait-list group in a 1:1 allocation ratio. Participants will be informed about the objectives, procedures, and potential benefits, and risks of the trial through standardized interviews prior to their participation and informed consent will be obtained from all participants. Participants will be allowed to withdraw from the study at any time without negative consequences and will be immediately notified when new information regarding the study is obtained. The personal information of the participants will be de-identified and will be accessible only to the investigators involved in this study. This follows the Consolidated Standards of Reporting Trials (CONSORT) Extension for Chinese Herbal Medicine Formulas 2017^[21]^ and Standard Protocol Items: Recommendations for Interventional Trials (SPIRIT) 2013 statement.^[22]^ In addition, the trial will be conducted in accordance with the Declaration of Helsinki and Good Clinical Practice Guidelines.

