#### Primary outcomes

2.8.1

The primary outcome measure is the total ISI score and will be measured at all visits. The primary endpoint is 4 weeks after treatment. The ISI questionnaire is designed to screen for the diagnosis and severity of insomnia through 7 items corresponding to the symptoms of insomnia. The total score ranges from 0 to 28, with 0–7 indicating no clinically significant insomnia, 8–14 indicating subthreshold insomnia, 15–21 indicating clinical insomnia (moderate severity), and 22–28 indicating clinical insomnia (severe). We will use the validated Korean version of the ISI questionnaire in this study.^[25,26]^

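### The two-sided significance level of the primary ISI analysis is printed as 0.5, very probably a misprint for 0.05, and should be corrected

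*Protocol article*

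**What the plan says.** Section 2.10 (Statistical analysis) names the outcome, the model and the level for the primary comparison. On the level it says: "A two-sided test with a significance level of 0.5 will be performed using an analysis of covariance". The model is specified "with the baseline as the covariate and the treatment group as fixed factors".

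This is the only significance level in the article, and nothing explains why a pilot trial should use such a liberal one. Earlier in the same section, the group summaries are to present "continuous data as mean and 95% confidence intervals or median according to the distribution of the data".

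Section 2.9 (Sample size) gives no significance level, power, effect size or standard deviation. It says that "a formal sample size calculation was not performed because this study will evaluate the feasibility of subsequent confirmatory randomized controlled trials".

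On the time point, section 2.10 says "The primary outcome is the total ISI score at 4 weeks post-treatment" and section 2.8.1 says "The primary endpoint is 4 weeks after treatment". Section 2.1 describes the course of the trial: "The trial period will include 4 weeks of medication (twice a day) and 2 weeks of follow-up".

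**The concern.** The level is a stated value for the primary analysis, so it is not a detail left to an analysis plan that we cannot see. A reader who takes the article as the public record of the primary test finds 0.5 and nothing that corrects it.

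At that level, the word 'significant' would attach to differences well within chance variation. This matters more here because participants are not blinded, the control is a wait-list and the primary outcome is a questionnaire score. The Discussion also says that a demonstrated effect is expected to support larger trials.

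The same figure can spill over. Section 2.10 allows covariates to be added when they differ significantly in demographic or social characteristics and gives no separate level for that judgement.

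**Working it through.** **Inputs from the article**
- Level 0.5, two-sided; ANCOVA with baseline and treatment group (section 2.10).
- 95% confidence intervals for group summaries (section 2.10), which correspond to 1 − 0.95 = 0.05.
- At least 12 per group, 20% dropout, 15 per group, 30 in total (section 2.9).

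**Step 1: the plan's own figure.** 12 / (1 − 0.20) = 15 per group, and 2 × 15 = 30. This matches section 2.9. No significance level enters the calculation, so the sample size neither supports nor contradicts 0.5 and does not change when the level is corrected.

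**Step 2: degrees of freedom.** The model estimates three terms: intercept, baseline and group. With 30 analysed, 30 − 3 = 27. With 24 analysed (20% lost), 24 − 3 = 21.

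**Step 3: critical values.** A two-sided test at level α rejects when |t| exceeds t(1 − α/2, df).

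| Analysed | df | α = 0.5 | α = 0.05 |
|---|---|---|---|
| 30 | 27 | 0.684 | 2.052 |
| 24 | 21 | 0.686 | 2.080 |

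**Step 4: error rates when SYM has no effect.** The test rejects with probability α, split evenly by direction, so a false finding in favour of SYM has probability α/2.
- α = 0.5: 50% show a significant difference; 0.5 / 2 = 25% favour SYM.
- α = 0.05: 5% show a significant difference; 0.05 / 2 = 2.5% favour SYM.

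A simulation of 100,000 null trials at each size agrees. The baseline correlation of 0.5 is an assumption and does not affect the null rejection rate.

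| Per group | α | Any significant difference | Favours SYM |
|---|---|---|---|
| 15 | 0.5 | 50.0% | 25.1% |
| 12 | 0.5 | 50.0% | 24.9% |
| 15 | 0.05 | 4.9% | 2.5% |
| 12 | 0.05 | 4.8% | 2.4% |

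**Step 5: smallest difference that would be significant.** In units of the residual standard deviation, and with baseline balanced between groups, this is t × √(2/n).
- 15 per group: 0.684 × √(2/15) = 0.25, against 2.052 × √(2/15) = 0.75.
- 12 per group: 0.686 × √(2/12) = 0.28, against 2.080 × √(2/12) = 0.85.

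**Step 6: time point.** The Abstract places data collection at baseline and at 2, 4 and 6 weeks after allocation. Section 2.8.3 labels the post-treatment phase as week 4. Medication lasts 4 weeks (section 2.1), so week 4 is the end of treatment and the only visit that fits the wording of the primary endpoint.

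**The case against.** The strongest reply is that this is a dropped zero in an exploratory pilot and that little depends on it. Much of that is fair. The misprint reading is by far the most likely. The estimate and the p value from the ANCOVA are the same whatever level is printed; only the label 'significant' changes. The 95% intervals in section 2.10 summarise each group and are not intervals for the treatment difference, so they point to 0.05 without formally contradicting 0.5. None of this makes the printed level right, and nothing else in the article corrects it.

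Three stronger readings are tempting, and the article does not support them.

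- **SYM would be declared effective in half of null trials.** Half is the rate for a significant difference in either direction. The test is two-sided, so about a quarter would favour SYM and about a quarter the wait-list.
- **The primary time point is week 8, or can be moved to week 6.** Read literally, 4 weeks of treatment plus 4 weeks afterwards gives week 8, for which the article describes no visit. The Abstract and section 2.8.3 resolve this to week 4, and nothing labels week 6 as primary. The wording is loose, but the endpoint is not open.
- **This test decides whether the larger trial goes ahead.** The Discussion only expects a demonstrated effect to provide a basis for further trials. Section 2.8.4 rests the feasibility of a full-scale trial on recruitment, adherence and completion rates.

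**Conclusion.** The point holds as an error in the printed significance level of the primary analysis. As written, the threshold for |t| falls from 2.05 to 0.68 at 27 degrees of freedom. The null rate of a significant difference rises from 5% to 50%, and the rate of falsely favouring SYM rises from 2.5% to about 25%. Each rate is ten times the conventional one.

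These figures assume that 0.5 is applied literally, that 24 to 30 participants are analysed, and that the usual ANCOVA assumptions hold. That 0.05 was meant is an inference from the 95% intervals and from the absence of any rationale for 0.5; the full protocol is not available to confirm it. The practical harm is limited by the pilot purpose and by the likelihood that the analysis will use 0.05 in any case. The correction is still needed, because this figure is the only level the article gives for its primary test.

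**What to change.** - In section 2.10, replace 0.5 with 0.05 (two-sided), after checking the figure against the full protocol. If a relaxed level was really intended, say so and justify it.
- Report the primary result as the adjusted mean difference in ISI score with its 95% confidence interval, so that the reading does not rest on a significance label.
- Optional: in the Abstract and sections 2.8.1 and 2.10, state the primary time point as week 4 after randomisation (end of treatment).

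The cost is one corrected figure and, if adopted, a few words on the time point. It needs no extra participants, data or visits, and the sample size stays at 15 per group. Whether the full protocol or the registry entry carries the same figure cannot be seen from the article and should be checked at the same time.

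### LOCF analyses a week-2 ISI as an observed week-4 score and can bias the week-4 difference in either direction; separately, the set labelled intention-to-treat is a modified one

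*Protocol article*

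**What the plan says.** All of the analysis text is in section 2.10 of the protocol article.

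- Endpoint: "The primary outcome is the total ISI score at 4 weeks post-treatment".
- Primary model: a test "using an analysis of covariance with the baseline as the covariate and the treatment group as fixed factors".
- Missing data: "The last observation carried forward method will be used for missing data". No condition or restriction is attached.
- Analysis set: the sentence opens "According to the intention-to-treatment principle, which analyzes all participants who have been randomized" and continues "all data obtained from participants who undergo an outcome measurement at least once after randomization will be included in the effectiveness analysis".
- Mixed model: "Furthermore, we will use a mixed effect model to identify trend changes".

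Elsewhere, the Abstract (Methods) sets data collection at baseline and weeks 2, 4 and 6, and section 2.8.1 has the ISI taken at every visit. Section 2.6 states that participants cannot be blinded. Section 2.9 sets 15 per group, "anticipating a 20% dropout rate".

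**The concern.** LOCF assumes that a participant's ISI would have stayed where it was at the last visit. Here that visit is week 2, halfway through a four-week course, so the assumption is that nothing changes over the second half. The article gives no support for this. Further change is plausible in both arms: entry requires an ISI of at least 15, and both groups receive sleep-hygiene education.

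Unequal dropout is also plausible. Allocation is open, only the SYM group can leave because of effects of the granules during the study, and the wait-list group is offered SYM only after its waiting period. The direction of any bias therefore cannot be assumed to be conservative. The ANCOVA also treats a carried-forward score as a measured one, so the standard error takes no account of the imputation.

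The analysis set is a separate matter. One sentence equates intention-to-treat with everyone randomised and then leaves out anyone with no measurement after randomisation. Readers of the results would take the label at its word.

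What is at stake is the preliminary estimate of effectiveness, which is one of the trial's stated aims.

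**Working it through.** **1. The plan's own figure.** Section 2.9 starts from 12 per group and allows for 20% dropout: 12 / (1 - 0.20) = 15 per group, 30 in total. This reproduces. It implies 0.20 x 15 = 3 dropouts per group, 6 of 30. The sample size is not affected by this point.

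**2. Who is imputed.** With visits at weeks 2, 4 and 6:
- Lost before week 2: no post-randomisation measurement, so excluded rather than imputed.
- Lost between weeks 2 and 4: the week-2 ISI is carried to week 4.
- Lost after week 4: the primary endpoint is already observed.

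**3. LOCF illustration.** The article gives no ISI trajectory, so the following mean changes from baseline are assumptions: SYM -3 at week 2 and -6 at week 4; wait-list -1.5 and -3. The true week-4 difference is -6 - (-3) = -3.0. Let d be the share of an arm lost between weeks 2 and 4, unrelated to outcome:

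LOCF mean = (1 - d) x week-4 change + d x week-2 change

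| Lost, SYM / wait-list | SYM mean | Wait-list mean | Difference | Bias |
|---|---|---|---|---|
| 3/15, 3/15 | 0.8(-6) + 0.2(-3) = -5.4 | 0.8(-3) + 0.2(-1.5) = -2.7 | -2.7 | +0.3 |
| 5/15, 1/15 | (10/15)(-6) + (5/15)(-3) = -5.0 | (14/15)(-3) + (1/15)(-1.5) = -2.9 | -2.1 | +0.9 |
| 1/15, 5/15 | (14/15)(-6) + (1/15)(-3) = -5.8 | (10/15)(-3) + (5/15)(-1.5) = -2.5 | -3.3 | -0.3 |

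Relative to 3.0, the effect is 10% too small, 30% too small and 10% too large.

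**4. When the bias vanishes.** Bias = -(dS x cS - dW x cW), where c is the mean change from week 2 to week 4 in SYM (S) and wait-list (W). With dS = dW and cS = cW it is zero.

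**5. Wider check.** The planned ANCOVA with LOCF was simulated with 15 per arm and 4000 runs. Assumed were an SD of 4 and correlations of 0.5 (baseline, week 2), 0.7 (weeks 2, 4) and 0.4 (baseline, week 4). Dropout was either unrelated to outcome or more likely with a high week-2 ISI; each pair below gives the bias in that order.
- SYM 18, 15, 12 and wait-list 18, 17, 16: +0.39 and +0.41 with 3 lost per arm; +1.19 and +1.59 with all 6 lost from SYM.
- Both arms 18, 16, 14, so no true effect: 0.01 and -0.01 with 3 per arm; -0.80 and -1.19 with all 6 lost from wait-list.
- SYM 18, 13, 15 and wait-list 18, 17, 16: -0.61 and -0.59 with 3 per arm.

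The full range is about -1.2 to +1.6 ISI points. In the third case LOCF favours SYM even with equal dropout.

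**6. Uncertainty.** If all 6 expected dropouts were imputed, the ANCOVA would use 30 - 3 = 27 residual degrees of freedom. The 24 participants with an observed week-4 score support 24 - 3 = 21.

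**7. Exclusion.** Dropping k of 15 participants whose true week-4 mean differs by e from the arm mean shifts that mean by -k x e / (15 - k). For k = 1, e = 2 the shift is -0.14; for k = 3, e = 4 it is -1.00; the signs reverse with e. A participant is either excluded or imputed, so these figures cannot be added to the LOCF figures for the same people.

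**The case against.** Several stronger readings are tempting, and the article does not support them.

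- **LOCF contradicts intention-to-treat.** It does not. It keeps participants with a missing week-4 score in the group to which they were allocated. Only the requirement of a post-randomisation measurement conflicts with the stated definition.
- **Baseline scores are carried to week 4.** This would be rare, since those lost before week 2 are excluded. It needs someone who misses weeks 2 and 4 and returns at week 6.
- **All of the 20% is imputed.** Section 2.9 gives no timing. Only losses between weeks 2 and 4 are imputed, so the illustration is the upper end of the equal-dropout case.
- **The effect and SD will size the next trial.** No section says so. The Discussion calls the results a base for later trials, and section 2.8.4 rests feasibility on recruitment, adherence and completion rates, which LOCF does not touch.

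It is also fair to say that the bias is modest beside the random error. With an assumed SD of 4, the unadjusted standard error of the difference is sqrt(2 x 16 / 15) = 1.46; a bias of 0.3 is about one fifth of that, and 0.9 is about 0.6 of it. Only the extreme simulated case (1.59) exceeds it. Sensitivity analyses and model details are commonly left to a fuller document, so their absence is not held against the article.

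All of this stands, and it narrows the point without removing it. LOCF is a method the article fixes, not one it leaves open, and a better analysis is already in the same section.

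**Conclusion.** The point holds in two separate parts.

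First, using LOCF for the week-4 ISI substitutes a mid-treatment score for the endpoint. The bias is possible, not certain. It can run either way, and its size depends on when people leave, from which arm, and how ISI moves after week 2. Under the labelled assumptions the estimate is -2.7, -2.1 or -3.3 against a true -3.0; over the wider assumed scenarios the bias runs from about -1.2 to +1.6 points. None of the trajectories, SDs or correlations comes from the article; the 20% dropout and 15 per group do. Imputed scores are counted as measured, so uncertainty is understated.

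Second, the effectiveness set is a modified ITT set under an intention-to-treat description. This is an inconsistency within one sentence of section 2.10.

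In a pilot with no power calculation, the consequence is a less reliable preliminary effect estimate. The change is worth making, but it does not threaten the trial's feasibility aims.

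**What to change.** - Take the primary week-4 ISI contrast from the mixed model already planned: ISI at all visits, group by visit, baseline adjusted for or constrained equal across arms, and small-sample degrees of freedom. Name a simpler covariance structure as the fallback if the unstructured one does not converge.
- Keep LOCF, if at all, as a labelled sensitivity analysis.
- Either include all randomised participants as allocated, or call the set modified ITT.

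**Cost.** Mostly wording, since the model is already in the plan. An unstructured covariance over four visits has 4 x 5 / 2 = 10 parameters, a real burden with 30 participants, hence the fallback. The model relies on missing at random, so it does not remove bias from dropout that depends on unobserved ISI. Participants with only a baseline score add almost nothing to the week-4 contrast. Including them makes the set match its label but does not recover the lost information.
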